#### Data dissemination

The study findings will be disseminated in open access, peer-reviewed journals and shared at international conferences. Research summaries, training tools, manuals, and other related resources were uploaded to the online knowledge management platform.

#### Data analysis

Data will be analyzed using SPSS software version 26.0 (IBM Corp, Armonk, NY). An intention-to-treat analysis (ITT) will be performed to explore the effectiveness of the trial. Patients in the treatment group will be included in the ITT analysis even if they had not completed the herb-partitioned moxibustion on the navel. Continuous variables that will meet the requirements for normal distribution will be represented as mean ± SD. Continuous variables that will not follow normal distribution will be represented as median and IQR. Categorical variables will be reported as absolute and relative percentage frequency. Independent Student *T*-test or Mann-Whitney *U* test will be used to explore differences in mean or median between the treatment group and the control group for continuous variables. Pearson *χ*^2^ test will then be performed to compare baseline characteristics and results for categorical variables. Paired sample *T*-test will be used to compare before and after treatment within-group differences. Multiple imputation will be used to process missing values in the data of this study. All tests will be two-tailed, and the significance level will be set as *P* < 0.05.

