## Abstract

**Background:**

Recurrent implantation failure (RIF) in the majority of patients undergoing in vitro fertilization and embryo transfer (IVF-ET) is caused by various factors such as maternal age, embryo quality, endometrial receptivity (ER), and immunity. The incidence of RIF is usually between 5 and 10%. Previous studies have shown that herb-partitioned moxibustion on the navel is one of the treatment methods of acupuncture with a positive effect on pregnancy. However, its application in the treatment of RIF has not been reported. Therefore, this study aims to evaluate the effectiveness and safeness of herb-partitioned moxibustion on the navel in improving the outcome of frozen embryo transfer (FET) in patients with RIF.

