## Introduction

### Background and rationale

Since the birth of the first test-tube baby in 1978, the technology of IVF-ET has been continuously innovated and developed. This innovation has made significant improvements in conception rate, implantation rate, and live birth rate. However, due to factors such as maternal age [1, 2], embryo quality [3], ER [4, 5], and immunity [6, 7], some patients who have received high-quality embryo transfers had unsuccessful pregnancy whereas more than 50% of the patients ended up with implant failure or biochemical abortion [8]. By definition, RIF is when women under the age of 40 years fail to achieve a clinical pregnancy after transplantation of at least four high-quality embryos in at least three fresh or frozen cycles [9, 10]. It has been reported that the incidence of RIF in IVF-ET patients may reach 5–10% [11], so RIF has become an issue of concern in current reproductive research.

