### Outcome measurements

#### Primary outcomes

The primary outcome is the rate of ongoing pregnancy. It is defined as a detectable fetal heartbeat after 12 weeks of gestation.

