#### Randomization and allocation

Participants will be randomly allocated into treatment or control groups at a rate of 1:1 by a computer-generated randomization sequence generated by the data coordinating center with SAS software version 9.2 (SAS Institute, Cary, NC). Allocation will be made by a designated researcher who will have no contact with any participant and will not be involved in the collection and analysis of the data. Due to the nature of the intervention, it will not be feasible to conceal the allocation from the practitioner and participants. The practitioner will not be allowed to disclose any information concerning their treatment to the participants or the assessor.

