#### Data management and monitoring

Three levels of data monitoring will be used to improve quality control. The reproductive medicine practitioner will make the trial and study plan available to all participant, and those who met the inclusion criteria and expressed interest in participating will sign the written informed consent form. The participant’s demographic information will be carefully recorded on the CRF. The supervisors will check the CRF for completeness and accuracy of input data. Any errors will be underlined, corrected, and signed by the corresponding investigator. An independent data monitoring committee (DMC) consisting of an epidemiologist, an acupuncture specialist, and a gynecologist will monitor and evaluate the recruitment of subjects, the progress of research implementation, and safety, confidentiality, and integrity of obtained data monthly. In addition, the DMC will regularly submit audit reports to the project management department. Further, it will provide recommendations for continuing the clinical trial, modifying the trial protocol, or terminating the trial.

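### The only test that fits ongoing pregnancy is an unadjusted chi-square; pre-specified adjustment for age and high-quality embryo number would gain a little precision at almost no cost

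*Protocol article*

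**What the plan says.** The Primary outcomes section states: "The primary outcome is the rate of ongoing pregnancy". Each woman either has a detectable fetal heartbeat after 12 weeks or does not, so the outcome is binary.

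The Data analysis section assigns tests by type of variable. For categorical data, a Pearson chi-square "test will then be performed to compare baseline characteristics and results for categorical variables". For continuous data it offers a parametric or a rank-based two-sample comparison, and says that the chosen "test will be used to explore differences in mean or median between the treatment group and the control group for continuous variables". All tests are two-tailed at 0.05. The section names no regression model and no covariate. No sentence singles out the primary test; that it is the chi-square follows from the general rule.

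The Abstract says that recurrent implantation failure "is caused by various factors such as maternal age, embryo quality, endometrial receptivity (ER), and immunity". The Background and rationale section repeats the list for unsuccessful transfers: "due to factors such as maternal age [1, 2], embryo quality [3], ER [4, 5], and immunity [6, 7".

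The eligibility criteria exclude women over 40 and require at least two high-quality embryos, so both items must be established before randomisation. Under Data management and monitoring, the participant's "demographic information will be carefully recorded on the CRF".

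**The concern.** Two features of the analysis text sit badly with the rest of the article.

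- **Unadjusted primary comparison.** The article names maternal age and embryo quality as drivers of failure and establishes age and embryo number at entry, but the treatment comparison uses neither. In a trial sized to just reach 80% power, any outcome variation that these variables explain is left in the error term.
- **Significance tests at baseline.** After sound randomisation every baseline difference is due to chance, so a test of it answers no useful question. Some significant results are to be expected, and the plan does not say what would follow from one.

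At stake is a modest amount of precision for the primary estimate, and a baseline table whose p-values tell the reader little.

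**Working it through.** **1. Reproduce the plan's sample size.**

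Inputs from the Sample size calculation section: 94 per arm, 80% power, a difference of 20% (read as 20 percentage points), two-sided Z test with pooled variance, alpha 0.05, achieved alpha 0.0496, 10% loss. The control rate is not given. A search over control rates points to 30% versus 50%.

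n = [1.960·√(2·0.4·0.6) + 0.842·√(0.3·0.7 + 0.5·0.5)]² / 0.20² = 93.0

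At n = 94 the normal approximation gives power 0.804. Exact binomial enumeration gives power 0.8002 and alpha 0.0496, the plan's own achieved level. Then 94/0.9 = 104.4, rounded up to 105 per arm and 210 in total. The figure reproduces, and it is the power of the unadjusted test: the uncorrected Pearson chi-square and the pooled two-sided Z test are the same test.

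**2. Power that adjustment could recover.**

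The documents give no covariate strength. Assume a combined SD of 0.3 to 0.7 for the covariates' contribution to the log-odds. The share of outcome variance explained is R² = Var(p(x)) / [p(1−p)], evaluated for marginal rates of 30% to 50%. Adjustment then acts roughly like an effective sample size of 94/(1−R²) per arm.

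| Log-odds SD | R² | R² used | Effective n per arm | Power |
|---|---|---|---|---|
| none | 0 | 0 | 94 | 0.804 |
| 0.3 | about 2% | 2% | 94/0.98 = 95.9 | 0.812 |
| 0.5 | about 5–6% | 6% | 94/0.94 = 100.0 | 0.828 |
| 0.7 | about 9–10% | 10% | 94/0.90 = 104.4 | 0.844 |

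The gain is 1 to 4 points of power, equal to about 2 to 10 more women per arm.

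**3. Check by simulation.**

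Logistic regression with two baseline covariates, 30% versus 50%, 94 per arm, 4,000 runs per scenario (Monte Carlo error about √(0.8·0.2/4000) = 0.6 points):

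- SD 0: 80.2% unadjusted, 80.1% adjusted. Nothing is lost if the covariates carry no information.
- SD 0.5: 79.3% unadjusted, 81.5% adjusted.
- SD 1.0, outside the assumed range: 80.4% unadjusted, 87.0% adjusted.

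With no treatment effect, overall rejection was close to 5% for both analyses in every scenario (0.042 to 0.053).

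**4. Baseline tests.**

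Under correct randomisation, the chance of at least one p < 0.05 among k independent tests is 1 − 0.95^k: 23% for k = 5, 40% for k = 10, 54% for k = 15. The article does not say how many characteristics will be tested.

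**The case against.** The strongest reply is that nothing here is wrong. The chi-square is valid for a 1:1 randomised binary outcome and agrees with the sample-size method. A reader might infer that a chance imbalance in age would bias the result or inflate false positives. The documents and the calculations do not support that: chance imbalance is ordinary sampling variation, already covered by the test's alpha, and overall type I error is near 5% with or without adjustment. In simulated null trials with a significant imbalance at SD 0.5, rejection was about 10% unadjusted and 8% adjusted, but on only about 200 trials, too few to show a difference. This part of the reply stands.

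Four further points stand.

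- **Size.** The gain is small and rests on an assumed covariate strength. Excluding women over 40 and requiring at least two high-quality embryos narrows the spread of both variables.
- **Prognostic factors.** The article names causes of failure; it does not show how strongly they predict outcome within this selected group. Previous failed cycles appear only in the definition of the condition, and nowhere as a prognostic factor.
- **Allocation.** A reader might infer that allocation ignores prognostic factors. The article says only that it is made "by a computer-generated randomization sequence generated by the data coordinating center"; silence on stratification in a condensed article is no defect.
- **Baseline p-values.** That they would lead to covariates picked after the fact is conjecture, since no rule links them to the outcome analysis.

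The reply fails in one respect. This is more than detail left to an analysis plan that is not shown: the article positively prescribes the baseline tests and a test without covariates for categorical results. A plan that adjusts its primary analysis would depart from that text.

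**Conclusion.** The point holds as a free improvement. The Data analysis section fixes an unadjusted chi-square as the only test applicable to ongoing pregnancy and tests baseline characteristics for significance, although the article itself names age and embryo quality as drivers of failure and establishes age and high-quality embryo number at entry. The consequence is forgone precision: power of about 81–84% with adjustment against about 80% without. This rests on the inferred 30% versus 50%, on 94 analysed per arm, and on the assumed log-odds SD of 0.3 to 0.7. The lower end is plausible given the eligibility limits. The planned test would not give an invalid result.

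**What to change.** Before outcome data are examined, amend the Data analysis section as follows.

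- Make the primary analysis a logistic regression of ongoing pregnancy on arm, age and number of high-quality embryos available at randomisation. Number of previous failed cycles is optional.
- Report the result as a standardised (marginal) risk difference with 95% CI, which keeps the 20-point scale of the sample-size calculation.
- Keep the chi-square as a supportive analysis.
- Describe baseline characteristics by arm without p-values.
- Do not adjust for anything that arises after randomisation, such as the number of embryos transferred.

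The cost is a change of wording, with no extra participants and no new measurements. One check is needed: eligibility requires only thresholds, so confirm that the CRF holds the actual age and embryo count, not just that the criterion was met. If an analysis plan already specifies such a model, bring the protocol text into line with it.

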**Assessments:**							
Serum estrogen					√	√	√
Serum progesterone					√	√	√
Ultrasonography	√	√	√	√	√	√	√
Pregnancy test					√	√	
Pregnancy outcome					√	√	√
Telephone follow-up						√	√

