#### Secondary outcomes

Secondary outcomes include the following six aspects: (1) endometrial type, (2) RI and PI of bilateral uterine artery and endometrial blood flow, (3) E_2_ and P, (4) biochemical pregnancy rate, (5) implantation rate, and (6) clinical pregnancy rate. The first three secondary outcomes will be compared with baseline in the mid-luteal phase of the third menstrual cycle. The first two secondary outcomes will be measured using transvaginal ultrasound and Doppler after the patient emptied the bladder and rested for 15 min (ultrasound with Siemens G50, probes 4/9 MHz) [29]. Biochemical pregnancy is defined as a positive pregnancy test result (serum β-hCG levels > 10 mIU/mL) 12 to15 days after FET. The implantation rate refers to the number of gestational sacs scanned by transvaginal ultrasound/ the total number of embryos transferred. Clinical pregnancy rate is defined as the presence of a gestational sac on ultrasound with fetal heart tones at 7 weeks of gestation.

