### Statistical analysis

#### Sample size calculation

The PASS software version 11.0 (NCSS, LLC. Kaysville, Utah, USA.) was used to estimate the sample size. According to a previous study [30], when the sample size of the treatment group and control group is 94 and 94 respectively, 80% of the power was achieved to detect the assumed rate of ongoing pregnancy in the untreated control group versus the effect size to be examined for (20%). The test statistic used was the two-sided *Z* test with pooled variance and the significance level of the test is 0.05. The significance level achieved in this design was 0.0496. The lost follow-up rate will be estimated by 10% and the final sample size of the treatment group and control group was 105 cases each and the total sample size was 210 cases.

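### For the secondary outcomes set against baseline, the only before/after test is within each arm; a baseline-adjusted comparison between arms should carry the treatment effect

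*Protocol article*

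**What the plan says.** The Secondary outcomes section lists six items. The first three are endometrial type; RI and PI of the uterine arteries with endometrial blood flow; and E2 and P. Of these it says: "The first three secondary outcomes will be compared with baseline in the mid-luteal phase of the third menstrual cycle".

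The Data analysis section then names the tests:

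- Within arms, a paired-sample t "test will be used to compare before and after treatment within-group differences".
- Between arms, an independent t or Mann-Whitney U "test will be used to explore differences in mean or median between the treatment group and the control group for continuous variables".
- For categorical variables, Pearson chi-square.
- Level: "All tests will be two-tailed, and the significance level will be set as" P < 0.05.

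No model that includes the baseline value is named. The section does not say whether the between-arm test is applied to third-cycle values or to changes from baseline.

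In Table 1, the row "Ultrasonography" is ticked at the first visit and at every later time point. The row "Serum estrogen" and the progesterone row, as the table reads in the text at hand, are ticked only in the fourth cycle, 14 days after transfer and 3 months after transfer.

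**The concern.** A paired test inside one arm answers whether that arm's mean moved. It cannot separate moxibustion from anything that moves both arms. Comparing the verdicts of two such tests (significant here, not significant there) is not a test of one arm against the other.

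A shift common to both arms is possible here. The follow-up is fixed in the mid-luteal phase, while no cycle phase is stated for the first-visit ultrasound. The documents do not show that the phases differ, so this is a possibility only. A between-arm contrast would cancel such a shift; a paired test would report it as change.

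Two things are at stake. Within-arm improvement on ultrasound measures could be presented as support for the mechanism when the arms do not differ. And the comparison that randomisation does support is planned without the precision that the scheduled baseline ultrasound could give it.

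**Working it through.** **Inputs.** From the Sample size calculation and Data analysis sections: 94 evaluable patients per arm, two-sided 0.05. Assumed, because the documents do not give them: correlation r between baseline and follow-up of 0.3, 0.5 or 0.7; equal SD at both times; a common change in both arms of 0.1 to 0.3 SD.

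**The plan's own figure.** The only stated figure is the sample size for the primary outcome. The control rate is not given. With an assumed 30% against 50%, the pooled-variance formula gives 93 per arm. Exact enumeration at 94 per arm gives a significance level of 0.0496 and power of 0.8002, matching the article. Then 94/(1 − 0.10) = 104.4, rounded up to 105 per arm, 210 in all. None of this depends on the secondary analyses.

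**Step 1: what paired tests show when moxibustion has no effect.** Let both arms have the same true change and let each paired test have power p. The arms are independent, so

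- P(significant in the treatment arm only) = p(1 − p). Its maximum is 0.25, at p = 0.5. At p = 0.8 it is 0.8 × 0.2 = 0.16.

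To put p on the scale of this trial: the SD of the change is √(2(1 − r)), which is 1 at r = 0.5, and the noncentrality is change × √94 / SD.

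| Common change (r = 0.5) | Noncentrality | Treatment arm significant | Treatment arm only |
|---|---|---|---|
| 0.1 SD | 0.97 | 16% | 13.5% |
| 0.2 SD | 1.94 | 48% | 25% |
| 0.3 SD | 2.91 | 82% | 15% |

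Over r = 0.3 to 0.7 and common changes of 0.1 to 0.3 SD, the treatment-only pattern ranges from 4% to 25%.

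**Step 2: precision of the between-arm comparison.** Relative to a test on follow-up values alone, the variance is 1 − r² for ANCOVA and 2(1 − r) for a change-score test. Power is for a difference of (1.960 + 0.842) × √(2/94) = 0.409 SD, at which the follow-up-only test has 80%.

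| r | ANCOVA variance | Cut | Change-score variance | ANCOVA power | Change-score power |
|---|---|---|---|---|---|
| 0.3 | 0.91 | 9% | 1.40 | 83.6% | 65.8% |
| 0.5 | 0.75 | 25% | 1.00 | 89.9% | 80.0% |
| 0.7 | 0.51 | 49% | 0.60 | 97.5% | 95.1% |

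Since 2(1 − r) − (1 − r²) = (1 − r)², which is never negative, ANCOVA is at least as precise as the change score. It is therefore the better choice whichever way the between-arm test is read.

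**Step 3: which outcomes this can be done for.**

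- RI, PI and blood flow: ultrasound is scheduled at the first visit and in the third cycle, so both values should exist.
- Endometrial type: its scale is not defined. If it is categorical, a paired t-test does not apply, and no before/after method for categorical data is named.
- E2 and P: the Secondary outcomes section needs a baseline and a third-cycle value; Table 1, as it reads here, schedules neither.

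**The case against.** The strongest reply is that a randomised between-arm comparison is already planned for every one of these outcomes, and that nothing in the article says a within-arm P value will be read as the treatment effect. Both statements are correct. The unadjusted between-arm test is valid and its type I error is not inflated; lack of adjustment costs precision only. The detail of a model is also something an article may leave to an analysis plan. But the paired test is not an omission: it is the method the article names for before/after data, for outcomes it defines against baseline.

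Some stronger readings are tempting, and the documents do not support them:

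- A reader might infer that baseline information is thrown away. If the between-arm test uses changes, baseline is used, only less efficiently. What is established is that it is not used for adjustment.
- A reader might quote 50% as the rate of misleading results. That is the maximum chance of significance in exactly one arm, and half of it is the control arm alone, which would not favour moxibustion.
- A reader might blame regression to the mean. The eligibility criteria do not select on RI, PI, E2 or P, so there is no clear ground for it.
- A reader might hold that the plan applies a t-test to a categorical variable. The article does not assign it to endometrial type; it assigns chi-square to categorical results. The gap is the missing before/after method.
- A reader might extend the point to the primary analysis. "The primary outcome is the rate of ongoing pregnancy", which is binary and has no baseline value. Adjusting it for age would be a separate, optional matter.

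**Conclusion.** The point holds for the first three secondary outcome groups. The one before/after test named does not estimate moxibustion against control. With equal change in both arms, it can show significance in the treatment arm alone up to 25% of the time, 16% when each paired test has 80% power. The planned between-arm tests are sound but unadjusted, and what they are applied to is left open. Baseline adjustment would cut the variance by 9% to 49% against a follow-up-only test. That range rests on assumed correlations of 0.3 to 0.7 and equal SDs; the 25% ceiling needs only independent arms with the same power in each paired test. The primary analysis and the sample size of 210 stand as they are.

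**What to change.** In the Data analysis section:

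1. For RI, PI and any continuous blood-flow measure, define the treatment effect as the between-arm difference from an ANCOVA of the third-cycle value on arm and baseline value, reported with its 95% confidence interval.
2. Report within-arm changes descriptively, without tests.
3. Define the scale of endometrial type. If it is categorical, compare arms by ordinal or multinomial regression with baseline type as covariate.
4. Reconcile the Secondary outcomes section with Table 1 on when E2 and P are measured. Use the same ANCOVA for them only if both a baseline and a third-cycle value are collected.

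Items 1 to 3 change wording only. SPSS, the named software, runs these models, and no added patients or, for the ultrasound outcomes, added measurements are needed. The cost of item 4 depends on which values are in fact collected. The change should be recorded before outcome data are compared by arm.
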